**METHODS**

*Design*

The study will employ a randomised controlled design to examine the effectiveness of a group-based ACT training programme for improving the well-being of NHS staff, compared to a wait-list control group.

*Participants*

Participants will be primary care staff within the NHS in Leeds and West Yorkshire. There will be one inclusion criterion: currently employed by the NHS and working within NHS primary care settings in Yorkshire and Humber. There will also be one exclusion criterion: not presently at work.

Based on sample sizes from other ACT studies in similar settings (e.g., Flaxman & Bond, 2010; Flaxman et al., 2016) we aim to recruit 140 people.

*Procedure*

Recruitment: The study will be advertised to potential participants via local awareness raising in primary care settings. Participants will be given information about the study and will be given the e-mail address of a member of the research team (NHS e-mail) to contact a member of the research team if interested in opting-in to the study.

Once participants have expressed an interest in the study, they will immediately be sent the participant information sheet (PIS) via e-mail, which outlines the nature of the research and training. After having had at least 24 hours to consider the information presented in the PIS, consent will be taken online. A consent form will be the first sheet of the pre-intervention questionnaire. Immediately after giving consent participants will then enter demographic details and generate their own individual participant number (First two letters of their mother's maiden name initials and the last four digits of their telephone number). This reference number will be used to complete all online questionnaire batteries.

Participants will be informed that they will shortly be randomly allocated to begin the training, the first session beginning in late September 2017, or to the waitlist control group. As soon as an initial 40 people have volunteered, the first randomisation process will take place, allocating volunteers to the ACT training programme or to the waiting list control group. Participants allocated to the training group will then receive dates, times, and locations of the scheduled training sessions. Participants will be randomised to groups by the research team using a computer generated randomisation procedure.

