Those allocated to the waiting list control will begin the training in Feb /March 2018. These participants will receive an email (or letter) providing reasons for being allocated to the later training group (i.e., limitations on the number of people that can be trained at one time, and the need to rigorously evaluate the impact of the training on staff well - being). All participants will be required to complete an online questionnaire battery (described in more detail below) on four separate occasions over the 14 week evaluation period. They will be e-mailed the questionnaire at the appropriate time-point, if they don’t complete the questionnaire within three days, they will be sent a reminder e-mail.

*Intervention*

The intervention will be based on an existing standardised ACT protocol designed for workplace settings. Participants will be invited to attend a total of four two-hour group sessions; these sessions will occur on four consecutive weeks.

Each session will consist of between 8 and 15 people. Training sessions will be delivered by experienced clinicians, who are also trained mindfulness teachers either on the national register or who comply with the Good Practice Guidelines. These trainers will be taught to deliver the study’s ACT intervention over a minimum of two training days with [name], who has extensive experience training professionals to deliver workplace interventions based around ACT. They will be supervised by [name] and by a professional mindfulness supervisor.

*Measurement*

A questionnaire battery will be administered to participants on four occasions:

1. Pre-intervention: minus 1 to 2 weeks

2. Mid-intervention: between sessions 2 and 3 of the intervention (week 3)

3. Post-intervention: one week after session 4 (week 5)

4. Follow-up: 3 months after post-intervention (week 19)

The questionnaire battery will take approximately 25 minutes to complete on each occasion. These on line questionnaires will be completed via encrypted survey software (known as Bristol Online Surveys) hosted by the CI’s institution (University of Leeds). Each participant will receive an email containing a link to the questionnaires. Those allocated to begin the training in in September 2017 will be e-mailed the questionnaires to complete prior to training.

*Primary outcome*

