1. General Health Questionnaire 12 (Goldberg & Williams, 1988). The GHQ-12 is one of the most widely used and well-validated measures of general well-being/mental health among working populations. The scale consists of a mix of positively and negatively worded items designed to capture various aspects of a person’s recent psychological functioning (e.g., sleep loss due to worry, ability to play a useful part in things, feeling able to face up to problems).

Higher scores indicate a higher level of psychological distress. As well as providing a primary overall measure of general mental health, the GHQ-12 can also be used to indicate the proportion of the sample that is experiencing clinically relevant level of distress.

*Secondary outcomes*

2. Shirom-Melamed Burnout Measure (SMBM; Shirom, 2003; Shirom & Melamed, 2006). The SMBM will be used to measure job-related burnout. This well-established 14-item scale has three subscales that are designed to capture core components of the burnout syndrome: physical fatigue, emotional exhaustion, and cognitive weariness. We selected this particular measure for the following reasons: (1) its theoretical underpinnings are clearly specified

(Shirom, 2003); (2) it explicitly seeks to capture a construct that is distinct from depression and anxiety; and (3) unlike more generic burnout measures, responses to the SMBM are temporally anchored to the past 30 work days.

3. Work-related worry and rumination during non-work time. Maladaptive perseverative cognition will be measured with the affective rumination subscale of the work-related rumination questionnaire (WRRQ; Cropley, Michalianou, Pravettoni, & Millward, 2012). This 5-item scale captures the degree to which a person is troubled by intrusive work-related thoughts during their leisure time. This subscale has demonstrated good psychometric properties among various samples of UK workers (Cropley et al., 2012; Querstret & Cropley, 2012). This measure will be supplemented with a 5-item work related worry and rumination scale developed and validated by Flaxman and colleagues (Flaxman, 2014; Flaxman et al., 2012). Participants will be asked to report amount of work-related worry/ rumination experienced during non-work time (e.g., evenings and weekends) over the past week.

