to take a balanced perspective on one’s experiences. We included this scale due to the growing interest in self-compassion as a potential mechanism of change in ACT (and other mindfulness-based) interventions, and the relevance of self/other compassion for professionals (such as GPs) working in healthcare settings (e.g., Cummings, 2014).

*Other measures*

Demographics questionnaire (age, gender, occupation, years in occupation, previous/current mindfulness practice).

*Analyses*

Hypothesis 1: Compared to a wait-list control group, those receiving ACT will have significantly better scores on outcome measures at all post-intervention time-points.

Here we will compare group scores between the control and ACT conditions at all time points using ANOVA. All available data will be included in the analyses, regardless of number of treatment sessions attended. This will involve an intention-to-treat (ITT) approach, with imputation of missing data by last value carried forward.

Hypothesis 2: Improvements in outcomes will be mediated by improvements in psychological flexibility in the ACT condition but not in the wait-list control condition. Here we will use mediation and moderation analysis to test whether change in the psychological flexibility processes helps to explain any changes in outcome variables. We will run this analysis to test if these effects are specific to the intervention group.

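### The Hypothesis 1 ANOVA does not use the pre-intervention score as a covariate, although it is collected for every outcome, so it is less precise than ANCOVA

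*Protocol*

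**What the plan says.** The protocol's Analyses section (Hypothesis 1) fixes the method: "Here we will compare group scores between the control and ACT conditions at all time points using ANOVA". The hypothesis itself is narrower: "those receiving ACT will have significantly better scores on outcome measures at all post-intervention time-points". The method therefore covers the pre-intervention occasion, about which the hypothesis says nothing. No covariate, change score or other use of the baseline value is named.

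Under Measurement, "A questionnaire battery will be administered to participants on four occasions", and the first of these is "Pre-intervention: minus 1 to 2 weeks". The pre-intervention value of the GHQ-12 and of every secondary measure is therefore available. The primary outcome is an overall GHQ-12 score ("Higher scores indicate a higher level of psychological distress"), which can be analysed as continuous.

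Under Participants, "we aim to recruit 140 people". This target is justified by the sizes of earlier studies. No alpha, power, effect size, SD or baseline-outcome correlation is given. Under Procedure, "Participants will be randomised to groups by the research team using a computer generated randomisation procedure", with no allocation ratio stated.

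**The concern.** In a randomised trial with a continuous outcome, the baseline value of that outcome is usually its strongest predictor. Using it as a covariate reduces the standard error and corrects the estimate for whatever imbalance chance has produced. The protocol collects this value and then names a method that does not use it in that way.

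The sentence has two natural readings, and neither is the best available:

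- **Separate ANOVAs at each occasion.** The baseline is ignored in the later comparisons, and a between-arm test is run at baseline. Under randomisation that test answers no question about the treatment.
- **Mixed group-by-time ANOVA.** The baseline is in the model, but as one more outcome. With one pre and one post measurement, the interaction test is equivalent to comparing change scores.

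At stake is the power of a trial of 140 people whose size rests on precedent, with no calculation to show that it has precision to spare.

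**Working it through.** **Plan's own figure.** The target of 140 cannot be reproduced, because the protocol gives no inputs for a sample size calculation.

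**Inputs.** From the protocol: total N = 140, a pre-intervention score on every outcome, ANOVA as the method. Assumed: 1:1 allocation (70 per arm), two-sided alpha 0.05, SD = 1 at each occasion, true effect d = 0.40, no dropout, and baseline-outcome correlation r from 0.4 to 0.7, with r = 0.3 as a less favourable case.

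**Variance of the arm comparison relative to separate ANOVAs**

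- Separate ANOVA, post score only: 1
- Pre/post group-by-time (change score): 2(1 − r)
- ANCOVA on baseline: 1 − r²

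The difference 2(1 − r) − (1 − r²) equals (1 − r)², which is positive for every r below 1. For r between 0 and 1, 1 − r² is also below 1. ANCOVA is therefore the most precise of the three on either reading. This ordering does not depend on d or N.

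**Power.** For a relative variance v, SE = √v × √(2/70) = √v × 0.169, and power ≈ Φ(0.40/SE − 1.96).

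- Separate ANOVA: 0.40/0.169 = 2.366, and Φ(0.406) = 65.8%. The t distribution gives 65.2%.
- ANCOVA at r = 0.5: SE = 0.866 × 0.169 = 0.146, 0.40/0.146 = 2.73, and Φ(0.77) = 78.0%.

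| r | 1 − r² | 2(1 − r) | Power, separate ANOVA | Power, group-by-time (pre/post) | Power, ANCOVA |
|---|---|---|---|---|---|
| 0.3 | 0.91 | 1.4 | 65.8% | 51.6% | 69.9% |
| 0.4 | 0.84 | 1.2 | 65.8% | 57.9% | 73.3% |
| 0.5 | 0.75 | 1.0 | 65.8% | 65.8% | 78.0% |
| 0.6 | 0.64 | 0.8 | 65.8% | 75.4% | 84.1% |
| 0.7 | 0.51 | 0.6 | 65.8% | 86.3% | 91.2% |

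**Detectable effect at 80% power.** Post score only: (1.96 + 0.84) × 0.169 = 0.474 SD. With ANCOVA this is multiplied by √(1 − r²): 0.434, 0.410, 0.379 and 0.338 SD at r = 0.4, 0.5, 0.6 and 0.7.

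**Equivalent sample size.** At r = 0.5, 140/0.75 = 187. Relative to post-only ANOVA, adjustment is worth about 47 more participants.

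**Chance imbalance (separate-ANOVA reading).** With 70 per arm, a baseline difference of up to 1.96 × 0.169 = 0.33 SD lies within the 95% range. At r = 0.5 it would shift a post-only estimate by about 0.5 × 0.33 = 0.17 SD, against an assumed effect of 0.40 SD.

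**The case against.** **ANOVA may mean the group-by-time model, and then baseline is not ignored.** This stands in part. With four occasions it is a natural reading, so it would be wrong to say that the plan certainly compares unadjusted scores. It also means that the step from about 65% to ANCOVA's power applies to one reading only. Against the pre/post interaction the gain is smaller at high r (86.3% to 91.2% at r = 0.7) and larger at low r (57.9% to 73.3% at r = 0.4). It does not vanish at any r in the range.

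**Covariates are commonly left to the statistical analysis plan.** That would answer a complaint that detail is missing. Here the protocol names the method, and a better one is available from data it already collects.

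**The unadjusted comparison is valid.** This stands. Under randomisation with a constant allocation ratio it is unbiased, and the protocol sets no power target that it misses.

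**The baseline may not be a clean covariate.** This needs an answer. Procedure makes the consent form the first sheet of the pre-intervention questionnaire, which puts baseline before allocation. Measurement says that people allocated to the September 2017 training will be e-mailed the questionnaires before it starts, which can be read as after allocation. A self-report given once the arm is known could be affected by that knowledge.

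A reader might also infer two stronger points that the document does not support:

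- *That the effect is diluted to three quarters of its size because baseline is averaged in.* This concerns a group main effect over all four occasions, a test the protocol never names. It also assumes a constant effect already complete at the mid-intervention measurement.
- *That omitting randomisation wave confounds arm with calendar time.* The text says only "As soon as an initial 40 people have volunteered, the first randomisation process will take place". Later rounds are implied, their number and timing are not given, and nothing says that the allocation ratio differs between them. The precision at stake is small: if waves explained 1% to 5% of the variance (assumed), power would move from 65.8% to between 66.2% and 68.0%.

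**Conclusion.** The point holds as one of efficiency. Whichever way the sentence is read, ANCOVA on the pre-intervention score is more precise than the named method for every r strictly between 0 and 1. With 70 per arm, two-sided alpha 0.05, a true effect of 0.40 SD, no dropout and r from 0.4 to 0.7, power at one time point is about 65% for separate ANOVAs, 58% to 86% for pre/post group-by-time, and 73% to 91% for ANCOVA. All of these inputs are assumptions. At r = 0.3 the variance gain over separate ANOVAs is only 9%.

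The planned comparison is not invalid or biased. It gives up precision and protection against chance baseline imbalance that could be had without recruiting anyone further. The change is worth making before outcome data are seen, because a covariate chosen afterwards would invite doubt.

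**What to change.** In the Analyses section, replace ANOVA for Hypothesis 1 with ANCOVA, or a mixed model, that compares the arms at each post-baseline time point with the pre-intervention score of the same measure as covariate. Apply it to the primary and all secondary outcomes. Drop the between-arm test at the pre-intervention occasion and report baseline scores descriptively.

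Reconcile Procedure with Measurement on when the baseline questionnaire is completed, and confirm that both arms complete it before allocation is known.

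A factor for randomisation wave is optional and secondary. It would matter mainly if the allocation ratio differed between waves, so stating the ratio would settle whether it is needed.

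The cost is about one sentence in Analyses and a clarification of questionnaire timing. No new data or participants are required.

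### Last value carried forward is the only missing-data rule for Hypothesis 1 and can bias the week-19 comparison in either direction, even with equal, random dropout

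*Protocol*

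**What the plan says.** The Analyses section of the protocol, under Hypothesis 1, sets three things for the outcome measures, including the primary GHQ-12:

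- The comparison: "Here we will compare group scores between the control and ACT conditions at all time points using ANOVA".
- The data included: "All available data will be included in the analyses, regardless of number of treatment sessions attended".
- The handling of missing scores: "This will involve an intention-to-treat (ITT) approach, with imputation of missing data by last value carried forward".

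The hypothesis itself is that "those receiving ACT will have significantly better scores on outcome measures at all post-intervention time-points", so the follow-up contrast is part of what is tested. The Measurement section places the last two questionnaires as "Post-intervention: one week after session 4 (week 5") and "Follow-up: 3 months after post-intervention (week 19").

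The section gives no assumption about why scores are missing, no alternative method and no sensitivity analysis, and nothing elsewhere in the protocol qualifies the rule.

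**The concern.** Carrying a score forward assumes that the person would have scored the same at every later questionnaire. That sits badly with a trial of a training programme meant to change scores, with a follow-up meant to show whether the change lasts. Someone who misses week 19 has the week-5 score, or an earlier one, entered as the follow-up result.

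Two errors pull in opposite directions. If the effect fades after training, carried week-5 scores keep part of it alive on paper and can support a false claim of maintenance. If the effect is real but some people have only a baseline score, carrying that score shrinks the effect, at week 5 as well as at week 19. Because the direction depends on trajectories and dropout that are unknown in advance, the rule cannot be defended as conservative. The imputed values also enter the ANOVA as if observed, so no uncertainty is attached to them.

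**Working it through.** **Inputs from the protocol.** Post-intervention at week 5 and follow-up at week 19, a gap of 19 − 5 = 14 weeks; recruitment target 140. The protocol gives no dropout rate, expected trajectory, SD, effect size or allocation ratio, so it has no figure of its own on this point to reproduce.

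**Assumptions.** 70 per arm (140 / 2, equal allocation); SD 1 at every visit; correlation 0.6 between visits; scores missing completely at random; a two-sample comparison at week 19 at the two-sided 5% level. Effects are given as size of benefit in SD units.

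**Formula.** If a share q of an arm misses week 19, the expected carried-forward arm mean is

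(1 − q) × (true week-19 mean) + q × (mean at the last observed visit).

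The bias is the difference in these means between arms minus the true week-19 difference.

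**1. Effect of 0.5 SD at week 5, gone by week 19; control flat; same q in both arms; all missing people last seen at week 5.** Reported effect = q × 0.5; true effect 0. Rejection rates come from 10,000 simulated trials per row.

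| q | Reported effect (SD) | Rejection, carried forward | Rejection, observed scores only |
|---|---|---|---|
| 10% | 0.05 | 5.9% | 5.0% |
| 20% | 0.10 | 8.7% | 4.8% |
| 30% | 0.15 | 14.0% | 5.3% |
| 40% | 0.20 | 21.1% | 5.2% |

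The last column is close to 5% because dropout was simulated as completely random. It is a benchmark, not the proposed remedy.

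**2. Partial fade, 0.50 to 0.20 SD, q = 30%, all last seen at week 5.** Reported effect = 0.7 × 0.20 + 0.3 × 0.50 = 0.29 SD.

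**3. As in 1 with q = 30%, but last visits spread evenly over baseline, week 3 and week 5 (assumed effects 0, 0.25 and 0.50 SD).** Reported effect = 0.10 × (0 + 0.25 + 0.50) = 0.075 SD. The standard error is √(2/70) = 0.169, so the shift is 0.075 / 0.169 = 0.44 standard errors, and rejection is about 7% to 8%.

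**4. Effect of 0.5 SD fully maintained; 10% to 40% of each arm with a baseline score only.** Reported effect = (1 − q) × 0.5 = 0.45 down to 0.30 SD.

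**5. No effect; both arms worsen by 0.3 SD between week 5 and week 19; 10% missing in control.** Spurious ACT benefit = (q in ACT − 0.10) × 0.3 = 0.03, 0.06 and 0.09 SD for 20%, 30% and 40% missing in ACT (rejection 5.3%, 6.2% and 8.1%). If both arms instead improve by 0.3 SD from baseline and baseline scores are carried, the same amounts count against ACT.

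**6. No effect at any visit and the same dropout pattern in both arms.** The carried-forward arm means are equal, so the bias is 0.

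**The case against.** The strongest reply is that nothing shows the bias will arise. It needs missing scores, and either an arm difference that changes after the last observed score or unequal dropout together with a time trend. Case 6 confirms this. A reader might infer that the rule is certain to bias the comparison, or always favours ACT. The protocol supports neither: case 4 shrinks a true effect.

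The size is also open to challenge. The 0.15 SD at 30% missing requires that every such person completed week 5. Spreading the last visits halves it to 0.075 SD, and at 10% missing the rejection rate hardly moves. This stands, so the result must be read as a range.

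Three further readings are tempting but not supported:

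- **Sickness absence.** The Participants section says "There will also be one exclusion criterion: not presently at work", and this governs entry. A reader might infer that people who later go off sick stop responding and keep a better, pre-absence score. The protocol does not say that they stop responding. If they did, their scores would probably be missing not at random, which the main remedy below would not cure by itself.
- **Process measures.** The rule stands under Hypothesis 1 only. No carried-forward rule is stated for the mediation analysis under Hypothesis 2.
- **Intention-to-treat.** Including people whatever their attendance is sound practice. The fault lies only in the imputation attached to it.

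On timing, the Procedure section speaks of questionnaires "on four separate occasions over the 14 week evaluation period", which does not fit a follow-up at week 19 and should be reconciled. The 14-week gap used here rests on the Measurement section's week labels. The bias formula does not contain the length of the gap, so the sizes do not depend on it.

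**Conclusion.** The concern holds in this form: the protocol fixes a rule that can bias the between-arm contrast in either direction, even when dropout is equal and random. It is a stated choice governing the primary outcome, not a detail left to an analysis plan.

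Under the assumptions listed, for a 0.5 SD effect lost by week 19, the false effect runs from 0.05 to 0.20 SD over 10% to 40% missing if everyone missing was last seen at week 5. It is about half that at 30% missing when last visits are spread evenly. Where the effect is maintained, the error is a dilution of 0.05 to 0.20 SD over the same range if only baseline scores are available. Confidence is high that the rule is fixed and unsuitable as the main method. The sizes are illustrations, since the protocol gives neither dropout nor trajectory.

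**What to change.** In Analyses, Hypothesis 1, keep everyone in the arm to which they were randomised whatever their attendance, and delete the carried-forward clause. In its place specify one of:

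- a likelihood-based mixed model for repeated measures on all observed scores, with arm-by-time terms and baseline included in the model; or
- multiple imputation under missing at random.

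Add one pre-specified sensitivity analysis for scores missing not at random, for example delta-adjusted imputation, because either main method rests on missing at random. Carried-forward values may stay at most as a further sensitivity analysis. This also fits the protocol's own intention to use all available data.

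The cost is a change of wording and slightly more analysis work, with no new data or participants. The calculations above show the fault in the present rule; they did not simulate the mixed model.
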